#### Patient allocation

Patients will be allocated to a control group (i.e., usual care) or the intervention group using an “On-Off” group assignment method (Figure 1) This method has been previously used in quality improvement studies [19-21], and meets study design quality criteria to permit inclusion in the Cochrane Collaborations’ Effective Practice and Organization of Care (EPOC) systematic reviews [22]. Conceptually, eligible PCN patients will enter a “recruitment pool” then allocated to the intervention or control group in sequential clusters. This recruitment cluster will be filled through a number of strategies, with an aim of 50 participants at a time. The first strategy will be through active identification of newly diagnosed patients on each of the PCN’s diabetes patient registry. It is recognized that not all newly diagnosed patients will be immediately identified through this registry and therefore as a second strategy, we will recruit newly diagnosed patients through other PCN referral registries (i.e., patients attending basic diabetes education classes). Newly diagnosed patients will be given priority entry into the intervention since they may be more likely to adopt new behaviours versus those having diabetes for a longer period of time.

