**Method:**

Using a non-randomized design, participants (total N = 110 per group) will be consecutively allocated in bi-monthly blocks to either a 6-month self-management program lead by an Exercise Specialist or to usual care. Our primary outcome is self-reported physical activity and pedometer steps.

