### Study subjects & recruitment

To satisfy the main objectives and achieve the study aims, we propose to implement and evaluate the HEALD program among recently diagnosed patients who are cared for within the PCN environment. One component of the PCNs management structure was the development of a chronic disease patient registry. More generally, a unique PCN patient registry will include information about the patient’s medical management and allow physicians and PCN staff to track patient progress. In keeping with the primary care network patient chronic disease management strategy (i.e., tracking), potentially eligible patients will be identified and recruited through a patient registry.

Following identification of potential study participants through each participating PCN, an endorsement letter from each PCN will be mailed to the potential participant by staff located at each PCN. Staff with this research responsibility within each of the PCN environments is intended to simulate real world chronic disease management practices (i.e., recruitment to available PCN programs). The endorsement letter was selected as a recruitment option after consultation with the PCN chronic disease management teams as a means to create a credible link between the PCN and their clients. Those interested in the study will be asked to contact the PCN by telephone where they will be prescreened to further determine eligibility. For those who have not responded by telephone within a specified time, a PCN staff member will perform a follow up phone call to determine interest and eligibility. Once an individual is deemed eligible, they will be sent a study package, which will include: a study information sheet endorsed by the local PCN physician lead for chronic disease management, a consent form and a pedometer with instructions. A baseline appointment will then be made with a trained Exercise Specialist to collect all relevant baseline clinical/laboratory information at each centralized PCN location using point-of-care instruments.

Inclusion criteria

· On primary care patient registry (i.e., under PCN physician care);

· 18-75 years of age or who are capable of sustained walking for 10 minutes;

· Diagnosed with type 2 diabetes (self-reported and confirmed through PCN patient registry);

· Received basic diabetes education since being diagnosed;

· Proficient English language skills.

Exclusion criteria

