**Figure 1 F1:**
[figure not shown]
Study flow diagram.

Cut-point dates will be set to stop filling the recruitment pool over a two-month time frame (i.e., bi-monthly block). If the recruitment cluster fails to fill with newly diagnosed patients (i.e., less than 50 eligible), a third strategy for recruitment will be implemented which will have the remaining program invitation spots randomly selected from a second pool of patients who were contacted through an earlier pre-screen mail out to all diabetic patients on the PCN patient registry.

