### Analytic strategy

All statistical tests will be two-sided with a level of significance set at 0.05 to evaluate the effectiveness of the intervention. Baseline comparisons will be performed using univariate analysis of variance (ANOVA) for continuous variables and chi-square analyses for categorical variables. The main analysis of our study is to compare the physical activity of the HEALD-PCN intervention (On) group participants to the usual care (Off) group, from baseline to 6 months as our primary assessment time-point. Employing the intention-to-treat (ITT) approach, we will also assess differences in group changes from: (1) baseline to 3 months, (2) baseline to 6 months, (3) and 3 months to 6 months using generalized linear mixed-model analysis (GLMM). GLMM uses all available data and provide a valid analysis when data are missing at random. The models will use baseline values for each outcome variable as a covariate to reduce the residual standard error and account for regression to the mean. Potential confounding variables (i.e., age, sex and BMI) will be included as covariates in the models. All data will be analyzed using Statistical Package for the Social Sciences v.20, SPSS Inc., Chicago Illinois, USA and Stata SE 10.1, StatCorp, College Station, Texas, USA.

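### The allocation text gives newly diagnosed patients priority into the intervention yet also describes a pool common to both arms; if the priority applies to On blocks only, the physical activity comparison can be confounded

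*Protocol article*

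**What the plan says.** The Abstract (Method) sets out the design: "Using a non-randomized design, participants (total N = 110 per group) will be consecutively allocated in bi-monthly blocks". Under Patient allocation, "eligible PCN patients will enter a “recruitment pool” then allocated to the intervention or control group in sequential clusters", with about 50 participants sought at a time. The first two strategies for filling a cluster look for newly diagnosed patients, in the diabetes registry and then in other PCN referral registries such as basic education classes. The paragraph ends: "Newly diagnosed patients will be given priority entry into the intervention since they may be more likely to adopt new behaviours".

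The third strategy, described after Figure 1, applies when newly diagnosed patients are too few. It has the "remaining program invitation spots randomly selected from a second pool of patients who were contacted through an earlier pre-screen mail out" that went to all diabetic patients on the registry. Patients with longer-standing diabetes can therefore enter. The relevant inclusion criterion is "Diagnosed with type 2 diabetes (self-reported and confirmed through PCN patient registry", with no limit on duration, although Study subjects & recruitment gives the aim as to "implement and evaluate the HEALD program among recently diagnosed patients who are cared for within the PCN environment".

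Under Analytic strategy, the model adjusts for the baseline value of each outcome, and "Potential confounding variables (i.e., age, sex and BMI) will be included as covariates in the models". Neither time since diagnosis nor recruitment source is named.

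**The concern.** Without randomization, the comparison is protected only by the allocation rule and the adjustment model. Read literally, the priority sentence makes entry to one arm depend on a trait that the protocol itself links to adopting new behaviours, and the primary outcome is a behaviour. If On blocks held a larger share of newly diagnosed patients, and those patients became more active whichever care they received, part of any 6-month difference would reflect who was enrolled rather than what the program did. Adjusting for baseline activity does not deal with this, because the stated difference lies in future change. The limitations in the Discussion concede a weaker design than a randomized trial but do not mention this imbalance. A larger sample would not remove it.

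**Working it through.** **1. The plan's own figures.** These are under Analytic strategy: f = 0.25, r = 0.5, power 0.90, two-sided alpha 0.05; for steps, 8,250 versus 6,500 with SD 3,300.
- Primary outcome: d = 2f = 0.5, and at r = 0.5 the SD of the change equals the raw SD. n = 2(1.960 + 1.282)²/0.5² gives 85 per group. The t-based version gives 86, as stated.
- Steps: n = 2(1.960 + 1.282)² × (3,300/1,750)² gives 75, as stated.
- Attrition: 86/0.8 = 107.5, so 108; 88/0.8 = 110, the stated total per group.

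The sample size is not in dispute.

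**2. The two readings of the allocation text.**
- *Priority for On blocks only.* The priority sentence names the intervention, not the study or the pool. The third strategy speaks of program invitation spots. No equivalent priority is stated for Off blocks.
- *Same rule for both arms.* Patients enter a pool and are then allocated. The recruitment strategies are attached to the cluster, whichever arm it becomes, and allocation is consecutive by two-month block, so the arm follows the calendar.

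Under the second reading, 220/50 = 4.4, so there are only about four or five clusters if 50 is the total per cluster. If the supply of newly diagnosed patients varies between blocks, the share filled by the third strategy varies too, and the arms can differ in either direction.

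**3. Size, if the arms differ.** Under no true effect:

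spurious difference = (difference between arms in share newly diagnosed) × (extra change in newly diagnosed patients under usual care)

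The document gives neither factor, so both are assumed. With SD 3,300 and 86 per group, SE = 3,300 × √(2/86) ≈ 503 steps/day. Type I error = Φ(b/SE − 1.96) + Φ(−b/SE − 1.96), where b is the spurious difference.

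| Imbalance in share | Extra change 500 | Extra change 1,000 | Extra change 1,750 |
|---|---|---|---|
| 0 points | 0 steps; 5.0% | 0; 5.0% | 0; 5.0% |
| 10 points | 50; 5.1% | 100; 5.5% | 175; 6.4% |
| 25 points | 125; 5.7% | 250; 7.9% | 438; 14.0% |
| 50 points | 250; 7.9% | 500; 16.8% | 875; 41.3% |

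Against the 1,750-step target, these non-zero differences run from 50/1,750 = 3% to 875/1,750 = 50%.

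**4. Do the named covariates help?** Trials with no true effect were simulated: 4,000 per scenario, 86 per group, baseline–follow-up correlation 0.5, 1,000 extra steps/day in newly diagnosed patients in either arm, and these patients assumed 4 years younger.

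| Share newly diagnosed, On vs Off | Model | Bias (steps/day) | Type I error | SE |
|---|---|---|---|---|
| 50% vs 50% | Baseline, age, sex, BMI | 6 | 4.8% | 446 |
| 50% vs 50% | plus diagnosis status | 6 | 5.0% | 441 |
| 75% vs 50% | Baseline, age, sex, BMI | 252 | 9.3% | 446 |
| 75% vs 50% | plus diagnosis status | 14 | 5.2% | 457 |
| 75% vs 25% | Baseline, age, sex, BMI | 480 | 19.5% | 447 |
| 75% vs 25% | plus diagnosis status | 3 | 5.2% | 510 |

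At 75% versus 25% the expected bias is 0.5 × 1,000 = 500, and the named covariates remove only about 20 of it. The 19.5% exceeds the 16.8% in the grid because baseline adjustment shrinks the SE but hardly touches the bias.

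**The case against.** The strongest reply is that the mechanism as described does not depend on the arm. The pool is filled newly-diagnosed-first, then allocated by calendar block, and nothing says that Off blocks are filled differently. A reader might infer as fact that On blocks will hold more newly diagnosed patients and Off blocks more long-standing ones. The document does not establish that, and Figure 1, which illustrates the assignment, is not shown. This part of the reply stands, and it limits the point to a contradiction plus its consequence under one reading. It does not make the priority sentence harmless, because that sentence names the intervention alone.

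Second, greater readiness to change may mean a larger response to the program. That would be effect modification, not confounding, and would create no false positive under no true effect. This also stands as a limit: the bias needs newly diagnosed patients to change more under usual care too. The stated reason neither says so nor restricts the readiness to the program.

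Third, a reader might take the covariate list as closed because it is introduced by i.e. The article uses the same abbreviation in the nutrition paragraph for a single example of a bread swap, so the list is not shown to be exhaustive. What remains is that it names three potential confounders and leaves out the one its own priority sentence points to.

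Fourth, the upper figures rest on strong assumptions. An extra change of 1,750 steps/day without the program equals the whole effect used to size the trial for steps.

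**Conclusion.** The allocation text supports two incompatible readings and must be reconciled. If the priority applies to On blocks only, the physical activity comparison can be confounded, probably in favour of HEALD, and the named covariates would not correct it. If it applies equally to both arms, the systematic imbalance largely disappears. Differences by arm across four or five clusters remain possible, in no predictable direction.

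The size is conditional: about 5% to 41% type I error over the assumed grid, and 5% if there is no imbalance or if the extra change occurs only under the program. The statement that the comparison is confounded goes further than the document allows.

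A reader might also extend the argument to HbA1c. The text does not support that, because the reason given for the priority concerns behaviours, and nothing says that newly diagnosed patients have a larger change in HbA1c.

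**What to change.** - **Patient allocation, including the third strategy after Figure 1:** state that the newly-diagnosed-first priority and all three recruitment strategies apply identically to filling On and Off blocks. Replace the reference to priority into the intervention with priority into the recruitment pool.
- **Analytic strategy:** add time since diagnosis (or newly diagnosed yes/no) to the named covariates. Add recruitment source as well if it is not collinear with diagnosis status; the third strategy comes into play only when newly diagnosed patients run short, so the two may nearly coincide. Compare both by arm at baseline.

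The cost is wording, one or two covariates that should be obtainable from the PCN registry and recruitment records, and no extra patients. Precision falls modestly if the arms are imbalanced: in the assumed 75% versus 25% scenario the SE rises from about 447 to 510 steps/day (510/447 = 1.14). Even then, 1,750/510 − 1.96 = 1.47, a power of about 93% for the steps target with 86 per group. With balanced arms there is no loss.

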**Figure 1 F1:**
[figure not shown]
Study flow diagram.

Cut-point dates will be set to stop filling the recruitment pool over a two-month time frame (i.e., bi-monthly block). If the recruitment cluster fails to fill with newly diagnosed patients (i.e., less than 50 eligible), a third strategy for recruitment will be implemented which will have the remaining program invitation spots randomly selected from a second pool of patients who were contacted through an earlier pre-screen mail out to all diabetic patients on the PCN patient registry.

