### Setting & population

This research will be carried out in four non-urban Primary Care Networks (PCNs) in Alberta, Canada. All PCNs are stand-alone physician-led corporations established to support family physicians through allied professionals, including: Chronic Disease Management Nurses, Registered Dietitian, Pharmacists, Health Promotion and Prevention Coordinators and Exercise Specialists. According to the Alberta Diabetes Surveillance System, the prevalence of diabetes in the province of Alberta was 5.5% in 2009 with approximately 20% over the age of 65 [17]. In the four participating PCNs, approximately 9,000 adult patients with diabetes are under the care of approximately 140 General Practitioners.

All PCNs in the current study provide some form of basic diabetes group education either through a group-based workshop or one-on-one counseling with a Registered Dietitian and/or Exercise Specialist by physician referral. It is recognized, however that these approaches to support lifestyle self-management are most likely insufficient to achieve and maintain lifestyle changes in the longer term. Thus, the HEALD program is intended to be an enhanced follow-up behavioral support program, prescribed for patients who have already received some form of basic diabetes self-management education. The HEALD-PCN evaluation will be over and above the baseline self-management education through a pragmatic controlled trial [18].

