##### Physical activity behaviours

Our primary outcome is self-reported physical activity, assessed with the Godin Leisure Time Exercise Questionnaire (GLTEQ) [28], modified to calculate MET minutes values [29] for total moderate and vigorous physical activity. The GLTEQ asks participants to report the average number of times per week, in the past month, they engaged in vigorous (rapid heartbeats, sweating), moderate (not exhausting, light perspiration) and mild (minimal effort and no perspiration) intensity PA, for a minimum of 10 minutes per session. Participant responses for the moderate and vigorous activity categories will be added together to calculate moderate and vigorous physical activity (MVPA) minutes per week and will serve as our primary self-report outcome measure.

For walking specific behaviors, pedometers (Yamax SW-200) and step logs will also serve as an objective measure of our primary outcome. Participants in both the intervention and control groups will be provided with a pedometer, and instructed to wear it and record total daily step-counts in a log for 3 consecutive days including one weekend day. The step log also allows for the collection of brisk steps for the intervention group. Self-reported walking will also be assessed using questions form the International Physical Activity Questionnaire (IPAQ) long version [30]. Participants will be asked, “During the last 7 days on how many days did you walk for at least 10 minutes at a time to go from place to place” or “in your leisure time”. Participants will then be asked, “How much time did you usually spend on ONE of those days walking from place to place” or “walking in your leisure time”. Responses will be recorded in days, hours, and/or minutes per day. A walking score will be calculated by multiplying the number of walking days by the walking minutes then by 3.3 (the MET value suggested for walking) to obtain walking scores in MET-minutes. Stages of physical activity behaviour change measures (≥ moderate levels) initially developed by Reed and colleagues [31] will serve as a secondary behavioral outcome (to assess stage transition).

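### Consecutive two-month On/Off blocks with no calendar term in the model leave season partly confounded with treatment for steps and MVPA

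*Protocol article*

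**What the plan says.** The Abstract (Method) says that "participants (total N = 110 per group) will be consecutively allocated in bi-monthly blocks". Patient allocation adds that patients are "allocated to the intervention or control group in sequential clusters", "with an aim of 50 participants at a time". The text after Figure 1 in the same section sets the block length: "Cut-point dates will be set to stop filling the recruitment pool over a two-month time frame". The setting is four non-urban PCNs in Alberta.

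Outcomes are taken at baseline, 3 and 6 months (Study measures). They include past-month leisure activity and a pedometer record in which participants "record total daily step-counts in a log for 3 consecutive days including one weekend day" (Physical activity behaviours).

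Analytic strategy makes baseline to 6 months the main comparison and uses the baseline value of each outcome as a covariate. It then states: "Potential confounding variables (i.e., age, sex and BMI) will be included as covariates in the models". No month, season, block or PCN term is named. The limitations in the Discussion mention the weaker non-randomized design and the vague definition of usual care, but not season.

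**The concern.** As written, the date of enrolment decides the arm. Each participant's baseline and 6-month measures fall in months set by the block, so On and Off participants are measured at different points of the year. If walking and leisure activity vary with season, which is plausible in non-urban Alberta but not quantified in the article, part of any arm difference is seasonal.

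The usual defence, that baseline is a covariate, works the wrong way here. Six months is half an annual cycle, so a group measured in a favourable season at baseline is measured in an unfavourable one at the primary time point. Subtracting a multiple of the baseline difference then adds to the seasonal difference. The bias could pass for a program effect or hide one, depending on the start month.

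**Working it through.** **The plan's own figure.** Steps: n = 2 × (1.96 + 1.2816)² × (3,300/1,750)² = 2 × 10.51 × 3.556 = 74.7, so 75 per group, as stated. With 20% attrition, 110 per group leaves 110 × 0.8 = 88 completers.

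**Inputs from the article.** Two-month blocks; 220 participants in all; clusters of about 50; r = 0.5; SD 3,300; planned difference 1,750 steps/day.

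**Assumptions.** Steps follow a 12-month sine wave of amplitude A (half of peak to trough). Enrolment is even within a block. Blocks alternate On, Off, On, and so on, with all PCNs in step. The baseline slope is 0.5, taken from r = 0.5. A is not in the documents; 300, 500 and 1,000 are used as a range.

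**Number of blocks.** 220/50 = 4.4, so 4 to 5 blocks, or 8 to 10 months: less than a full year.

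**Seasonal difference at one time point.** Averaging the wave over a two-month block shrinks it by sin(30°)/(π/6) = 0.955. Block midpoints lie at 30°, 90°, 150° and 210° of the cycle. On (30°, 150°) averages to the vector (0, 0.5). Off (90°, 210°) averages to (−0.433, 0.25). The difference has length √(0.433² + 0.25²) = 0.5. The maximum at one time point is 0.5 × 0.955 = 0.48A. A fifth block at 270° gives the same 0.48A.

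**Baseline adjustment.** The difference at 6 months is minus the difference at baseline, D. Adjusted bias = −D − 0.5D = −1.5D, so the maximum is 1.5 × 0.4775A = 0.72A. The average over start dates is 0.716A × 2/π = 0.46A.

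**Type I error.** SE = 3,300 × √(2/88) × √(1 − 0.5²) = 431 steps. Two-sided error = Φ(bias/SE − 1.96) + Φ(−bias/SE − 1.96). The average column takes the mean of this over start dates.

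| A (steps/day) | Max bias (% of 1,750) | Average bias (% of 1,750) | Type I error, worst | Type I error, average |
|---|---|---|---|---|
| 300 | 215 (12%) | 137 (8%) | 0.08 | 0.06 |
| 500 | 360 (20%) | 228 (13%) | 0.13 | 0.09 |
| 1,000 | 715 (41%) | 456 (26%) | 0.38 | 0.22 |

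**Sensitivity to the block layout (maximum adjusted bias).**
- Two blocks, which is what 50 per PCN would imply: 1.43A.
- Four or five equal blocks: 0.72A.
- Blocks of 50, 50, 50, 50 and 20: 0.62A.
- Six equal blocks (one full year): 0.
- Eight equal blocks: 0.36A.

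**Cost of adjustment.** Regressing arm on annual sine and cosine terms gives variance inflation of 1.10 (four blocks) and 1.17 (five). Then 75 per group becomes about 83 to 88. With a second harmonic the inflation is 1.8 to 2.6. With one On and one Off block, the annual terms alone inflate it by about 4.5.

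The step figures cannot be carried over to MVPA, for which the article gives no mean or SD. The mechanism is the same.

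**The case against.** Several points on the other side stand.

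- **Everything scales with an assumed amplitude.** No seasonal figure appears in the article, and across the range used the effect goes from minor to serious.
- **The worst start date is not the expected one.** At A = 300 to 500 the average bias is 137 to 228 steps. The planned 1,750 is about 4 standard errors (1,750/431), so a shift of that size would not overturn a real effect of the planned size.
- **The block structure is loose.** Fifty is an aim, and the text does not say whether it is per PCN or overall. Six equal blocks averaging about 37 (220/6) would cancel an annual cycle exactly; two blocks would double the bias.
- **Figure 1, which illustrates the allocation, is not shown.** It could bear on whether the PCNs are staggered. The text does not say that they are.
- **The covariate list may not be exhaustive.** The article elsewhere uses i.e. to introduce an illustration, and the full model may be in a document not shown.
- **The design's weakness is admitted**, and the On-Off method is defended by its acceptance for EPOC reviews. Neither point deals with season.

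A reader might infer that treatment and season are wholly confounded, or that the test's error rate is 0.38. The documents support neither. On and Off blocks interleave, so the confounding is partial, and 0.38 needs both the largest assumed amplitude and the least favourable start date. The change-score factor of 0.95A is also not relevant, since the planned model uses baseline as a covariate.

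**Conclusion.** The point holds as a should-fix. The allocation text ties arm to two-month calendar blocks, and the covariates that the article names do nothing about calendar time. Followed as written, season is partly confounded with treatment for both parts of the primary outcome, and baseline adjustment raises the worst-case factor from 0.48A to 0.72A.

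For 4 to 5 equal blocks, the bias is 0.46A on average and 0.72A at most, in a direction set by the start month. This rests on an annual sine wave, alternating blocks in step across PCNs, a baseline slope of 0.5 and an amplitude that the documents do not give. The layout matters as much as the amplitude: the maximum runs from 0 to 1.43A across the block counts considered. The evidence does not show that the trial's conclusion would be wrong, only that the stated plan does not guard against a foreseeable bias that is cheap to remove.

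**What to change.** **Analytic strategy.** Record the date of every assessment. Add annual sine and cosine terms for that date, and PCN, to the steps and MVPA models.

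**Patient allocation.** Where scheduling allows, counterbalance the sequence: in each two-month block two PCNs are On and two are Off, and they swap at the next block. On and Off are then compared within the same season. This has to be settled before the blocks are run.

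**Block fixed effects.** Use them only if the PCNs are staggered. Otherwise each block belongs to one arm, block is nested in treatment, and the treatment effect cannot be estimated.

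**Cost.** Counterbalancing is a scheduling change. Without it, the annual terms inflate variance by about 1.10 to 1.17 with 4 to 5 blocks, taking 75 per group for steps to about 83 to 88, within the 88 completers expected from 110. The terms remove a smooth annual cycle; a more irregular pattern would be only partly removed, and a second harmonic costs much more. If only one On and one Off block are run, inflation is about 4.5 and adjustment is not practical, so season should then be stated as a limitation.
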